**Process evaluation measures**					
Implemen-tation measures	*Context, reach, dose delivered and received, fidelity/adaption, appreciation, and contamination*	Developed for study	Children + parents	– Baseline – Extra questionnaire – Short-term follow up	
	*Context, reach, dose delivered and received, fidelity/adaption, appreciation, and contamination*	Developed for study	Intervention coordinators	Start, mid, end intervention questionnaires	

The primary outcome is children's life satisfaction 1 year after completion of camp (long-term follow up), and will be measured in the child questionnaire by an adapted version of the Cantril ladder used in the HBSC study questionnaire (44). The outcome will be measured at all four time points.

The secondary outcome is self-reported BMI 1 year after completion of camp (long-term follow up). It will be measured objectively twice at the five health camps by the personnel on their scale at the beginning and end of the 10-week health camp (baseline, post health camp) and self-reported by the child in the questionnaires at all four time points.

### Sample Size Calculations

In total 1,038 children will attend the 10-week stay at one of the five camps during the recruitment period (see Figure 4). Approximately 288 will attend Liljeborg health camp and half (~144) will receive the extended maintenance intervention and the other half (~144) the standard maintenance intervention. The 750 children from the four other residential health camps are offered a standard maintenance intervention as well. We know from records at the health camps, that approximately 8% do not complete their stay at the camps. We do, however, have no knowledge of how many children turn down the offer of standard or extended maintenance.

**Figure 4 F4:**
[figure not shown]
Flowchart of expected numbers of participants.

Historically it has been difficult to reach a satisfactory response rate for the long-term follow up questionnaires as mentioned before (27).

We used already collected questionnaire data from the camps to calculate the number of children needed to detect changes on the primary outcome (see Table 3). We made a random retrieval of 50 children from each of the five health camps, a total of 250.

Based on this calculation, we found a SD of 2.1. A prospective power calculation shows that with 80% power, we will be able detect a difference of 0.53 points on the Cantril ladder between groups with 144 in the intervention group and 894 in the control group. These power calculations are based on the assumptions that all the children complete the stay at the camp and all the children allocated to the extended maintenance intervention at the Liljeborg health camp, will accept this. If we assume there is a 8% drop out of all health camps, the calculation with 132 in the intervention group and 822 in the control group, we will be able to detect a difference of 0.55 on the Cantril ladder, making it a very small difference.

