The effectiveness of the camps has been investigated earlier, mostly in smaller studies. In 2008, a study of intervention activities at the Skælskør camp found significant weight reductions by the end of the program compared to baseline (20). An program evaluation of two of the health camps concluded that parents lacked support in order to be able to change their own lifestyle and to support their children in the process of returning home after their stay at camp (26). Historically, DCSH has focused solely on the child and on the time spent at health camp. The earlier vision was to let the children return to their homes with new confidence in themselves, having experienced a remarkable change of lifestyle and self-confidence.

The findings from 2008 were supported by another evaluation of a project which was conducted at two of the camps, Skælskør, and Hobro from 2013 to 2016, with the aim of improving the collaboration between the camps, the families, and home municipalities. The evaluation concluded that the children benefitted greatly from the health camp with higher quality of life, increased belief in themselves, less bullying in their school environment, feeling healthier and losing weight. However, it also highlighted that the children would be expected to benefit more from a more extended collaboration between the health camp and the parents, schools, and municipalities. Due to low response rate with only 5% answering all the questionnaires including the long-term questionnaire 1 year after camp the evaluation had serious limitations especially on the long-term effects 1 year after camp (27).

Based on the recommendations from this evaluation, the two different maintenance interventions included in this study as intervention- and control group have been developed.

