### Protocol Amendment

All amendments to the protocol will be reported in the trial registration and be transparent in study papers.

We have already been obliged to introduce some amendments to the original trial registration due to the Covid-19 pandemic and modifications made by the intervention coordinators along the way. We originally planned to recruit children for a 52-week period but due to the fact that the Liljeborg camp initiated the online questionnaires faster than the other four health camps, we have extended the recruitment at Liljeborg camp with 10 weeks to obtain a larger intervention group. Furthermore, the covid-19 pandemic has influenced the recruitment period as the health camps have been locked down by the government twice during the year of recruitment along with shorter local lock downs due to outbreaks of covid-19 and periods of lower occupancy rates at the camps e.g., due to requirements from the government to have less people gathered in settings like this.

We originally planned to include objective measures of weight and height at baseline, post health camp and at the long-term follow-up at the Liljeborg health camp. However, due to the Covid-19 lockdown DCSH will not be able to gather all children at the Liljeborg health camp to participate in a reunion day 1 year after camp and obtain long-term objective measures of weight and height as originally planned. Instead, we must rely on self-reported measurements at all timepoints supplemented by findings on agreement between objective and self-reported measurements at baseline and post camp.

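### The stated 80% power for 0.53 or 0.55 points holds, in the unadjusted calculation given, only if every child counted answers the 1-year questionnaire

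*Protocol article*

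**What the plan says.** Sample Size Calculations takes the standard deviation from existing camp data on 250 children: "Based on this calculation, we found a SD of 2.1". For a power of 80% it then states: "we will be able detect a difference of 0.53 points on the Cantril ladder between groups". The group sizes behind this figure are 144 intervention and 894 control children. Two assumptions are named for it: all children complete the camp stay, and all those allocated to the extended intervention accept it. Response to the 1-year questionnaire is not among them.

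A second scenario removes 8% for children who leave camp early, giving 132 versus 822. For this the article concludes: "we will be able to detect a difference of 0.55 on the Cantril ladder, making it a very small difference".

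Elsewhere the article says the following:

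- **Outcomes:** the primary outcome is life satisfaction 1 year after camp.
- **Child Questionnaires:** response close to 100% is expected for the two questionnaires filled out at camp, among children who complete the stay. The 3-month and 1-year questionnaires go to parents by email.
- **Sample Size Calculations:** just before the power figures, it admits that satisfactory long-term response has been hard to reach.
- **Historical View, on an earlier two-camp project:** "Due to low response rate with only 5% answering all the questionnaires including the long-term questionnaire 1 year after camp", which it calls a serious limitation.
- **Inclusion and Data Analysis:** children who do not complete camp stay in the intention-to-treat analysis.

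**The concern.** The power calculation uses the number of children who enter or finish camp, whereas the primary comparison draws its information from children who answer a year later. The only loss removed, 8%, is of a different kind. Children who leave camp early remain in the intention-to-treat set, so leaving camp mainly dilutes the effect and does not measure 1-year non-response.

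A reader will take the study to be 80% powered for about half a ladder point. If many families do not answer, a null result could be read as evidence of no effect when a difference of that size could easily have been missed. Ethical Issues says that, if no effect is shown, the future and form of the intervention are uncertain, so the reading of a null result matters here.

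**Working it through.** **Inputs from the article:** SD 2.1; power 80%; group sizes 144/894 and 132/822; 8% camp non-completion. **Assumptions made here:** two-sided 5% (the article gives no significance level or sidedness) and the same 1-year response in both groups (the article gives no expected rate).

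**Step 1. Reproduce the stated figures.** Detectable difference = (1.96 + 0.84) × SD × √(1/n₁ + 1/n₂).

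- 144 versus 894: 2.80 × 2.1 × √(1/144 + 1/894) = 0.528, stated as 0.53.
- 132 versus 822: 2.80 × 2.1 × √(1/132 + 1/822) = 0.552, stated as 0.55.

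A one-sided 5% test would give 0.469 and 0.490, so two-sided 5% is the level that fits. The arithmetic is correct.

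**Step 2. Identify the loss removed.** 144 × 0.92 = 132.5 and 894 × 0.92 = 822.5. The 8% camp non-completion accounts for the whole reduction, so 1-year non-response is implicitly zero.

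**Step 3. Let 1-year response vary.** If a share q answers in each group, the detectable difference becomes 0.528/√q. Power for 0.53 is Φ(0.53·√q/SE − 1.96), with SE = 2.1 × √(1/144 + 1/894) = 0.189.

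| Assumed response | Responders | Detectable difference | In SD units | Power for 0.53 |
|---|---|---|---|---|
| 100% | 144 / 894 | 0.53 | 0.25 | 80% |
| 80% | 115 / 715 | 0.59 | 0.28 | 71% |
| 60% | 86 / 536 | 0.68 | 0.32 | 59% |
| 50% | 72 / 447 | 0.75 | 0.36 | 51% |
| 30% | 43 / 268 | 0.96 | 0.46 | 34% |

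**Step 4. Allow for baseline adjustment.** Data Analysis adjusts for baseline life satisfaction. With an assumed baseline-to-1-year correlation ρ, the SD becomes 2.1 × √(1 − ρ²), and the detectable difference scales with √((1 − ρ²)/q). The stated sensitivity is kept when q is at least 1 − ρ²: 91% response for ρ = 0.3, 84% for 0.4, 75% for 0.5 and 64% for 0.6. At 50% response, ρ would have to be about √0.5 = 0.71. With ρ = 0.5 the detectable differences in the table are multiplied by √0.75 = 0.866, giving about 0.51 at 80% response, 0.59 at 60%, 0.65 at 50% and 0.84 at 30%.

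**Step 5. Size of the stated difference.** 0.55/2.1 = 0.26 SD.

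**The case against.** The strongest reply is that the primary model adjusts for baseline life satisfaction while the stated calculation does not, so true power could be as good as claimed. This stands as a possibility: Step 4 shows that ρ = 0.5 with about 75% response would be enough. A reader might infer that the study will certainly lack 80% power, and the article does not support that. What it does show is that the figure depends on a response rate it leaves out, and that it neither gives nor uses a correlation that could make up the loss.

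Multiple imputation keeps every child in the analysis. It does not recover information on an unobserved 1-year score beyond what covariates and earlier scores predict.

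The 8% is not worthless as an allowance. Children who leave camp may also be harder to reach later, so counting them as lost is defensible as a partial allowance. It does not cover completers who fail to answer.

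The 5% figure is not a forecast. It is the share who answered all questionnaires in an earlier project at two camps, and this study plans reminders by email and, if needed, by phone, plus audio reading. It is evidence of difficulty only and is not used as a response rate above.

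A reader might also infer that every camp place is assumed filled, because 990 a year plus 48 equals 1,038. The article does not say so. The enrolment window under Inclusion, September 2019 to June 2021, is longer than the 52 weeks plus 10 at Liljeborg given under Protocol Amendment, so closure time may have been absorbed. What remains is that the basis of "In total 1,038 children will attend the 10-week stay at one of the five camps during the recruitment period" is unclear when "the health camps have been locked down by the government twice during the year of recruitment" and occupancy was reduced for periods.

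Nor does the article say that the result decides whether the intervention continues; it calls this uncertain. Figure 4, on expected participant numbers, is not available here and may show follow-up numbers, but they would not change the calculation given in the text.

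**Conclusion.** The point holds in this form. The arithmetic is right, but the 0.53 and 0.55 figures rest on full response at 1 year, a premise that the article's own account of long-term response undercuts. In the unadjusted calculation, 50% to 80% response means a detectable difference of about 0.75 to 0.59 and power for 0.53 of about 51% to 71%. At 30% response the figures are 0.96 and 34%. These rest on SD 2.1, a two-sided 5% test, the full 144/894 as starting numbers and equal response in both groups. Baseline adjustment may recover part or, with high response and a substantial correlation, all of the loss, but the article does not rely on it. Calling 0.55 points very small is a lesser matter of wording; 0.26 SD conveys the size better.

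**What to change.** Replace the 0.53/0.55 statement with a short table of detectable differences for the expected number of 1-year responders. It should:

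- cover a range of response rates, for example 30% to 80%;
- show each figure with and without an assumed baseline correlation, labelled as an assumption;
- give each difference in ladder points and in SD units, and drop the description as very small;
- state the significance level and sidedness;
- say that the 8% is camp non-completion, which under intention to treat is mainly a matter of dilution, and is not the allowance for 1-year non-response.

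Base the starting numbers on actual intake by camp. Reconcile the 1,038 with the enrolment window under Inclusion and with the 52 weeks plus 10 and the lockdowns under Protocol Amendment.

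The cost is a few sentences and a small table in the protocol and registration, and a less favourable power statement. Enrolment, outcome and analysis model do not change.

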### Data Analysis

We will use descriptive statistics to investigate baseline equivalence and loss to follow up. We will graphically visualize the development over time in both intervention group and control group 1 for the primary and secondary outcomes.

We will analyze the effectiveness of the extended maintenance intervention compared to control group 1 on the primary and secondary outcomes, using linear regression analysis and on explorative outcomes using logistic regression analyses. We will apply an intention-to-treat approach including all children in the intervention group they initially have been allocated to irrespective of whether they have completed the intervention or are lost to follow-up. Missing data will be replaced by multiple imputation. We will perform complete case analysis for sensitivity analyses.

The effect analyses will be adjusted for baseline factors including gender and age of the child, life satisfaction, BMI-*Z* score, and parental socioeconomic position.

For the total population at all five camps, we will calculate the standard deviation of the primary and secondary outcomes right after camp to calculate Cohen's *d* effect size.

Furthermore, we will perform sensitivity analysis restricted to the data from the Liljeborg health camp to identify any differences between camps (control group 2). We will investigate the association between intervention dose and effect (per protocol analyzes).

We will investigate if the effect differs by subgroups (see moderators in Figure 2).

We will summarize process measures using appropriate descriptive statistics including proportions, means (SD), and medians (IQR).

We will identify who is in most need of the intervention and find out who does not need the intervention.

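### Multiple imputation and its named sensitivity analysis, complete cases, both treat 1-year non-response as ignorable, so their agreement would not show whether the conclusion depends on outcome-related loss.

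*Protocol article*

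**What the plan says.** The Data Analysis section sets an intention-to-treat analysis that keeps children in their allocated group "irrespective of whether they have completed the intervention or are lost to follow-up". On missing values it states "Missing data will be replaced by multiple imputation", followed by "We will perform complete case analysis for sensitivity analyses". It states no missingness assumption and names no not-at-random variant.

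Two other planned items come close to the issue:
- Loss is to be described: "We will use descriptive statistics to investigate baseline equivalence and loss to follow up".
- There is a second "sensitivity analysis restricted to the data from the Liljeborg health camp to identify any differences between camps". Its stated target is camp differences, not missing data.

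On response, the historical section says of an earlier evaluation at two camps: "Due to low response rate with only 5% answering all the questionnaires including the long-term questionnaire 1 year after camp". The Sample Size Calculations section adds: "Historically it has been difficult to reach a satisfactory response rate for the long-term follow up questionnaires". That section allows only for 8% not completing the camp stay. It makes no allowance for questionnaire non-response at 1 year. Under Child Questionnaires, near-complete response is expected for the two questionnaires filled in at camp, while the 3-month and 1-year ones go to parents by e-mail.

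**The concern.** A sensitivity analysis for missing data is useful when it relaxes the assumption behind the primary analysis. Standard multiple imputation is valid if, given the observed data, response does not depend on the missing score. A covariate-adjusted complete-case regression with a missing outcome needs response not to depend on that outcome given the model covariates. If children whose life satisfaction has fallen back are less likely to answer, both analyses miss it, and close agreement between them could be taken as reassurance that it does not give.

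The primary outcome sits at the time point most exposed to this, and intention-to-treat brings every lost child into the primary result through imputed values. Response, and the reasons for non-response, could differ by group. Families are not blinded. Coordinator contact runs about 10 weeks after camp in the extended group and about 4 in the standard group. The provider that developed the intervention also manages data collection and reminders.

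**Working it through.** **Inputs from the protocol article.** SD 2.1; 80% power; 144 v 894 children, or 132 v 822 after 8% camp drop-out; detectable differences 0.53 and 0.55 ladder points (Sample Size Calculations). No alpha is given, so two-sided 0.05 is assumed. No expected 1-year response rate is given.

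**1. The plan's own figures.** Detectable difference = (1.960 + 0.842) × SD × √(1/n₁ + 1/n₂).
- 144 v 894: 2.802 × 2.1 × √(1/144 + 1/894) = 0.528, stated as 0.53.
- 132 v 822: 2.802 × 2.1 × √(1/132 + 1/822) = 0.552, stated as 0.55.

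Both reproduce, so 0.53 is a fair yardstick.

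**2. Bias under outcome-related loss.** Let r be the response proportion and d the number of points by which non-responders truly score below what the imputation model predicts. T is the intervention group and C the control group. Imputation puts each group mean too high by (1 − r) × d, so

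bias in the difference ≈ (1 − r_T) × d_T − (1 − r_C) × d_C.

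All r and d below are assumptions.

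| Case | Calculation | Bias |
|---|---|---|
| Equal response (50%), equal shortfall (1 point) | 0.5 × 1 − 0.5 × 1 | 0 |
| Intervention responds more (70% v 50%), equal 1-point shortfall | 0.3 × 1 − 0.5 × 1 | −0.20 (understated) |
| Intervention responds less (50% v 70%), equal 1-point shortfall | 0.5 × 1 − 0.3 × 1 | +0.20 (overstated) |
| 40% missing, 0.5-point shortfall in intervention only | 0.4 × 0.5 | +0.20 (overstated) |
| 50% missing, 1-point shortfall in intervention only | 0.5 × 1.0 | +0.50 (overstated) |

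For the bias to equal the whole 0.53, a shortfall in the intervention group alone must be 0.53/0.5 = 1.06 points at 50% missing, or 0.53/0.3 = 1.77 points at 30% missing. With an equal shortfall and a 20-point response gap it must be 0.53/0.2 = 2.65 points.

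**3. Would multiple imputation and complete case disagree?** A simulation used 144 v 894, SD 2.1, a true effect of zero, a baseline-outcome correlation of 0.5, response of about 62-65% v 50%, 600 runs and 20 imputations. The imputation model held group and baseline score only. Intervention-group response was made to depend on the unseen 1-year score; control response was not.

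| Log-odds of response per SD of 1-year score (intervention) | Mean complete-case estimate | Mean imputation estimate | False positives | Mean absolute gap between the two |
|---|---|---|---|---|
| 0 | 0.01 | 0.01 | 6% | 0.02 |
| 0.5 | 0.27 | 0.27 | 27-28% | 0.02 |
| 1.0 | 0.50 | 0.50 | 66-67% | 0.02 |

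The gap between the methods is the same with no bias and with a bias of 0.50. In this setting their agreement carries no information about outcome-related loss.

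**4. The other planned items.** The descriptive look at loss can show that response differs by group or by observed scores, but not that it depends on the unseen 1-year score. The single-camp analysis uses the same kind of data and carries the same assumption.

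**The case against.** **This is conventional, and a fuller analysis plan may add more.** Multiple imputation with a complete-case check is a common pair, and the article does not word it as exclusive. The contents of the imputation model are fairly left to an analysis plan, and that part is not pressed here. What stands is that the article itself names the sensitivity analysis for missing data, and the one it names largely shares the primary assumption.

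**The two methods need not agree.** The ladder is measured four times, and a parent-reported ladder and WHO-5 are collected too. If the imputation model uses these while the complete-case model adjusts only for baseline factors, the results could diverge. This is correct, and the simulation did not include such data. But divergence would reveal dependence on observed data only.

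**No analysis can detect not-at-random loss.** Also correct. A reader might infer that the plan is at fault for failing to detect it, or that a tipping-point analysis would. Neither follows: such an analysis shows only how far the conclusion moves under stated departures.

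**The 5% is not a 1-year response rate.** A reader might infer that about 95% of primary outcomes will be imputed. The figure is the share answering every questionnaire in an earlier two-camp project, and e-mail and telephone reminders are planned here. It shows that the risk is known, not its size.

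**Overstatement is not the natural direction.** A reader might infer that the benefit will be exaggerated by up to 0.50 points. That needs a shortfall among intervention non-responders and none among controls, and nothing in the document supports that asymmetry. Longer coordinator contact would more naturally raise intervention response, and with equal shortfalls the effect is then understated. Extended contact also ends about 10 weeks after camp, some 42 weeks before the 1-year questionnaire.

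**Conclusion.** The point holds in a limited form. As the Data Analysis section stands, the named check on missing data rests on essentially the same ignorability assumption as the primary analysis. The plan therefore has no stated means of showing how far the primary conclusion depends on loss related to the unseen 1-year ladder score.

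Size and direction cannot be settled from the document, which gives no 1-year response rate and no information on non-responders. Under the assumptions shown, the bias runs from zero, through 0.20 points in either direction, to an overstatement of 0.50 in an assumed extreme case, against 0.53 detectable. The document does not support a claim that the result will be biased, or biased towards benefit. The change is worth making because it is cheap and long-term response is a weakness the authors themselves report.

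**What to change.** - Keep multiple imputation as the primary analysis.
- Add a delta-adjusted (pattern-mixture) tipping-point analysis of the 1-year ladder. Shift the imputed values by a pre-stated grid, for example 0 to −2 points (about one SD of 2.1), varied separately in the two groups so that unequal departures are covered. Report the combinations at which the conclusion changes.
- Keep complete case as a supplementary analysis, and say that its agreement with imputation is not evidence against outcome-related loss.

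Cost: a few lines in the plan and some programming, with no new data. The downside is one more analysis to report, and a conclusion that may look less certain.
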